### Association of site characteristics and practices with outcomes

To identify factors contributing to outcome variation between networks, detailed information will be obtained on health service provision, including units’ physical layout, environmental characteristics, human factors, and management practices at the national and site level. The type of data and strategy for collecting this information will be determined following the comparison of outcomes between networks to target identified problem areas and evaluate the culture, context, and practices of each network. Factors with possible impact on outcome differences between and within networks will be ascertained using a variety of tools, such as surveys, recurring questionnaires, and in specific instances, site visits to explore details if permitted.

The data will be pooled across sites and networks, and statistical analyses will identify factors significantly associated with outcomes. Through a collaborative process, findings will be discussed with members of participating networks to select physical and environmental factors, human and resource factors, or processes of care that can be modified through a quality improvement process. Each network will then implement practice changes within these three main target areas according to their outcome priorities and the constraints of their respective health care systems.

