#### Care-provision factors

Clinical practices represent the third and possibly most important set of characteristics that likely contribute to variation in outcomes. Variations in clinical practices are well known among neonatal communities [8]; however, no systematic prospective approach has determined, compared, and benchmarked variations associated with outcomes. Some of the key practice variations between centers and networks include referral practices (inborn vs. outborn) [62-64], differential use of the type of initial respiratory support [65-67], types and timings of surfactant administration [68], fluid management [69], timing of initiation of parenteral nutrition [70], use of donor milk, management of patent ductus arteriosus [71], availability and use of echocardiography, use of prophylactic interventions [72] (e.g., probiotics, high frequency oscillatory ventilation, phototherapy, and L-arginine), and the scope of involvement of parents.

Specific to each secondary outcome we will identify ‘top’ performing networks and networks with significant room for improvement. Subsequently, working groups of interested stakeholders from each network will be formed to determine methods to identify possible care provision practices related to such variations. Study methods will be similar to those described earlier, and will include annual snapshot surveys of each unit, detailed questionnaires specific to practices (e.g. parental presence, use of donor milk, diagnosis and management of hypotension, etc.), and in certain instances of outstanding success, a site visit with structured exploration of the practices in question. All methods of exploration will be conducted with directions from the iNeo Governing Board and Scientific Advisory Committee to protect privacy and confidentiality. Because individual unit information will not be disclosed to the iNeo Coordinating Centre, individual networks will be asked to identify willing members for such participation.

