#### Statistical analyses and power for identification of practice and service variation

Associations of clinical management practices and other external factors with outcomes will be assessed under the general framework of individual patient-level data meta-analyses. Random-effects models with adjustment for confounding variables and important risk factors will provide estimates of association and quantify residual variation due to unknown or unmeasured unit-specific and network-level factors. These analyses will identify treatment practices and health care services with significant impact on outcomes, which subsequently can be targeted for implementation or improvement by specific units or networks. This information along with details of the practices/factors will be made available to initiate discussion within the iNeo community regarding data-informed, evidence-linked potentially better practices. Analyses (two-sided tests) based on 10,000 yearly admissions evaluating impact of treatment/practices (assuming 50% exposure) on outcomes (incidence 1% to 40%) will be able to detect relative risks of 1.6 to 1.1 with statistical power of 80% and 5% type I error rate. This is a conservative power calculation based on data expected to be collected in a one-year timeframe.

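### Site visits are reserved for high-performing units; if their findings enter the pooled exposure data, practice associations are biased toward apparent protection

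*Protocol article*

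**What the plan says.** The order of work matters here. Under *Care-provision factors*, the plan first separates, for each secondary outcome, the top "performing networks and networks with significant room for improvement". Working groups then decide how to find the practices behind the differences. The methods named are "annual snapshot surveys of each unit, detailed questionnaires specific to practices" and, "in certain instances of outstanding success, a site visit with structured exploration of the practices in question". Because the coordinating centre does not know which unit is which, "individual networks will be asked to identify willing members for such participation".

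Under *Association of site characteristics and practices with outcomes*, the tools for ascertaining factors are given as "such as surveys, recurring questionnaires, and in specific instances, site visits to explore details if permitted". The next paragraph begins: "The data will be pooled across sites and networks, and statistical analyses will identify factors significantly associated with outcomes".

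The model is described under *Statistical analyses and power for identification of practice and service variation*: "Random-effects models with adjustment for confounding variables and important risk factors will provide estimates of association". No term for how a practice was ascertained is mentioned. Practices found to be associated with better outcomes are then put to sites for adoption (*Implementation and evaluation of practice changes to improve outcomes*).

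**The concern.** Read together, these sections let the intensity of exposure measurement depend on the outcome. A unit chosen for its good results may have its practices examined on site. An average or poor unit answers surveys and questionnaires, and no visit to such units is planned for care practices. A practice that a visit finds but a form misses would be recorded as present in the good unit and absent in another unit that does the same thing.

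This is exposure misclassification that differs by outcome. Case-mix adjustment does not address it, because the error lies in the exposure and not in an omitted confounder. Random effects do not remove it either, since a unit-level practice is compared between units. At stake is whether the list of practices proposed to sites includes some that only look beneficial.

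**Working it through.** **The plan's own figure.** The power statement gives detectable relative risks of 1.6 to 1.1 for incidence 1% to 40%, with 10,000 admissions, 50% exposure, 80% power and two-sided 5%. With 5,000 exposed and 5,000 unexposed infants, and incidence taken as the unexposed rate, the detectable relative risk is 1.64 at 1% and 1.07 at 40%. The plan's figures are reproduced to one decimal. They are infant-level relative risks of the outcome, so any artefact has to be judged on that scale.

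**Inputs.** From the plan: 50% exposure, 10,000 admissions, incidence up to 40%. Assumed, because the document gives no value:
- true relative risk 1, with the same true use π = 0.5 in visited and other units;
- visits detect all users; surveys and questionnaires detect a share s = 0.5, 0.7 or 0.9; no false positives;
- visited units hold a share f = 0.05, 0.10 or 0.20 of infants;
- the outcome rate in visited units is k = 0.5 or 0.7 times the rate r elsewhere.

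**Formulas.** Recorded as exposed: fπ in visited units and (1−f)πs elsewhere. Recorded as unexposed: f(1−π) and (1−f)(1−πs).

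Rate in recorded exposed = r·[fπk + (1−f)πs] / [fπ + (1−f)πs]

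Rate in recorded unexposed = r·[f(1−π)k + (1−f)(1−πs)] / [f(1−π) + (1−f)(1−πs)]

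The spurious relative risk is the first divided by the second; r cancels.

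**Results.**
- Mild case (f = 0.05, k = 0.7, s = 0.9): exposed (0.0175 + 0.4275)/0.4525 = 0.9834; unexposed (0.0175 + 0.5225)/0.5475 = 0.9863; ratio 0.997.
- Middle case (f = 0.10, k = 0.5, s = 0.7): exposed (0.025 + 0.315)/0.365 = 0.9315; unexposed (0.025 + 0.585)/0.635 = 0.9606; ratio 0.970.
- Extreme case (f = 0.20, k = 0.5, s = 0.5): exposed (0.05 + 0.20)/0.30 = 0.8333; unexposed (0.05 + 0.60)/0.70 = 0.9286; ratio 0.897.

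All 18 combinations fall below 1. Inverted, the middle case is 1/0.970 = 1.03 and the extreme case 1/0.897 = 1.11. Only the extreme case passes the plan's smallest detectable effect (1.07 computed, 1.1 stated).

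**Chance of a false protective finding** with 10,000 infants, against a nominal 2.5% in that direction:

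| Overall incidence | Middle case | Extreme case |
|---|---|---|
| 10% | 7.0% | 36.3% |
| 20% | 11.0% | 68.2% |
| 40% | 22.5% | 97.8% |

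The mild case stays near nominal (3.3% at 40% incidence). These chances ignore clustering by unit and so are upper-end illustrations.

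**Check of the remedy.** With s = 1, so that ascertainment is equally complete in visited and other units, both rates equal r(fk + 1 − f) and the ratio is 1.00 for every f and k.

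**The case against.** The strongest reply is that the decisive step is inferred. Bias arises only if visit findings supplement or overwrite the exposure field in the pooled model, and no sentence says that they will. The phrase "in specific instances, site visits to explore details if permitted" also fits a qualitative role, and every unit is to be surveyed. Purely exploratory visits would cause no bias. This stands, and it makes the point conditional. It does not dispose of it: the same sentence names visits as a means of ascertaining factors, the next paragraph pools the data, and nothing excludes visit findings. Unit anonymity is no barrier to linkage, because each network both codes its units and names the willing ones.

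A second reply is that collection methods are openly deferred and an article condenses the full plan. That covers how visit information is coded. It does not cover who is visited and why, which this article does state.

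Third, the harm is limited. The quality-improvement method also draws on published evidence and each site's own baseline data, and implemented changes are re-evaluated every 6 to 12 months. This stands as a limit on consequences, but it does not correct the association estimate.

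A reader might also infer a much larger artefact by comparing recorded practice between top and other units. With 50% true use, all top units visited and 70% survey detection, that odds ratio is (0.50/0.50)/(0.35/0.65) = 1.86. It runs from 1.22 at 90% detection to 2.33 at 60%. The arithmetic is right, but these are unit-level odds ratios of recorded practice and cannot be set against infant-level relative risks of 1.6 to 1.1. Visiting all top units also contradicts the text, which limits visits to certain instances and willing, permitted units, and low survey detection gives no credit to the detailed questionnaires.

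**Conclusion.** The point holds in conditional form. As written, the plan lets exposure measurement depend on outcome and has no rule keeping the more intensive measurement out of the pooled models. If visit findings enter them, the bias has a known direction, toward apparent protection. It is not a general bias away from the null: for a harmful practice it moves the estimate toward or past the null.

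The size is unknown, because the share of infants in visited units and the accuracy of the surveys are not given. Over the assumed ranges the spurious relative risk is 0.997 to 0.897, with 0.970 in the middle. It is negligible if few units are visited or the surveys are accurate, and usually smaller than the effects the plan can detect. It matters mainly for common outcomes, where a shift of about 3% can raise the false-positive rate noticeably before clustering is allowed for. The documents do not support saying that practices will look protective when they are not, or that the artefact is as large as the effects sought.

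**What to change.** In *Association of site characteristics and practices with outcomes* and in *Care-provision factors*:

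1. State that site-visit findings only generate candidate practices and are not used as exposure data in the pooled models.
2. Add each candidate practice, in identical wording, to the next annual snapshot survey of all units.
3. Estimate associations only from items collected the same way in every unit, using the survey answers for the visited units as well.

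The cost is a few sentences and a few items in a survey that is already planned; no further visits are needed. The downside is the wait for the next survey round. The overview sets the end of 2014 for identifying associations and mid 2015 for implementing changes, so a practice first noticed on a late visit might miss the first cycle. It could join a later one, since several cycles are planned over two and a half years.

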#### Statistical analyses and power for identification of practice and service variation

Associations of clinical management practices and other external factors with outcomes will be assessed under the general framework of individual patient-level data meta-analyses. Random-effects models with adjustment for confounding variables and important risk factors will provide estimates of association and quantify residual variation due to unknown or unmeasured unit-specific and network-level factors. These analyses will identify treatment practices and health care services with significant impact on outcomes, which subsequently can be targeted for implementation or improvement by specific units or networks. This information along with details of the practices/factors will be made available to initiate discussion within the iNeo community regarding data-informed, evidence-linked potentially better practices. Analyses (two-sided tests) based on 10,000 yearly admissions evaluating impact of treatment/practices (assuming 50% exposure) on outcomes (incidence 1% to 40%) will be able to detect relative risks of 1.6 to 1.1 with statistical power of 80% and 5% type I error rate. This is a conservative power calculation based on data expected to be collected in a one-year timeframe.

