#### Human and resource factors

Human factors and available resources represent another aspect of care provision possibly associated with differences in outcomes. However, associations between human and resource factors and neonatal outcomes have not been thoroughly investigated, particularly not on a national scale. Human factors include staffing in relation to day and night shifts [33,55], weekdays versus weekends [56], ratio of nurses to patients [57], pattern of work for medical and nursing staff (hours on call, total duration of active duty time over 4 week period, etc.), number and types of trainee doctors, allied healthcare personnel coverage, constitution of attending team for high-risk births, and relative expertise of the health care providers attending resuscitation of extremely preterm infants considering their overall experience in direct patient care, training, and research.

Neonatal outcomes are also impacted by resource availability and utilization, specifically volume and capacity. Units with high volume are reported to have better outcomes compared with units with low volume, possibly due to relatively increased staff experience [58,59]; however, it has also been noted that low volume units may be less crowded and have reduced rates of complications [60]. Alternatively, these differences may be secondary to centralization of care rather than volume, as seen in data from Finland [61]. Similarly, units functioning at >90% capacity at all times, irrespective of volume, may have different outcomes compared with units operating at lower capacity.

Data on human factors and resource utilization will be collected using snapshot surveys administered at the unit level. Due to likely variations from year to year, data on human factors and resource utilization will be collected on an annual basis using electronic tools (such as recurring auto-filled surveys based on previous responses so as to only report changes), and while the data may not capture variation in the daily activity levels or acuity in the unit, this will represent the average condition.

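### The practice-outcome power figures assume independent infants, so calling them conservative is not supported for exposures shared by a whole unit

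*Protocol article*

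**What the plan says.** The protocol article, under *Statistical analyses and power for identification of practice and service variation*, bases its calculation on this: "Analyses (two-sided tests) based on 10,000 yearly admissions", "assuming 50% exposure" and outcome incidences of 1% to 40%. It concludes that the analyses "will be able to detect relative risks of 1.6 to 1.1 with statistical power of 80% and 5% type I error rate". It then characterises the result: "This is a conservative power calculation based on data expected to be collected in a one-year timeframe". The short time window is the only reason given. No number of units, ICC or design effect appears.

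The same section plans random-effects models, partly to quantify variation between units and networks that measured factors leave unexplained.

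The preceding sections say how the exposures will be measured. Under *Human and resource factors*: "Data on human factors and resource utilization will be collected using snapshot surveys administered at the unit level". *Physical and environmental factors* also relies on a one-off survey of units. *Care-provision factors* uses yearly unit surveys together with practice questionnaires and some site visits.

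**The concern.** A unit's layout, staffing pattern or unit-wide policy takes one value for every infant treated there. Information about its effect then depends largely on how many NICUs stand on each side of the comparison, not only on how many infants they admit. A calculation that treats 10,000 infants as 10,000 independent observations is optimistic for such an exposure. The section itself expects outcomes to vary between units beyond what is measured, so a between-unit correlation of zero does not fit its own model.

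At stake is how realistic the plan is for the second network objective, which is to identify site characteristics and care practices associated with outcomes. The results feed the choice of practices for implementation. A reader told that the figure is conservative will expect real power to be at least as good as stated.

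**Working it through.** **Inputs from the article.** 10,000 admissions; 50% exposure, so 5,000 per group; incidence 1% to 40%; two-sided 5%; 80% power. Table 1 yearly admissions: 3,500 + 2,700 + 1,500 + 3,700 + 2,600 + 900 + 800 + 7,700 = 23,400. Network NICUs: 29 + 30 + 23 + 73 + 36 + 7 + 9 + 44 = 251. Infants per unit-year: m = 23,400 / 251 = 93.2.

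**Assumption.** The article gives no ICC, so a range is shown.

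**Step 1: reproduce the stated figures.** Two independent proportions with n per group, unexposed rate p0, exposed rate p1 = p0 × RR and mean rate p̄:

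power = Φ{ [ (p1 − p0) − 1.96 √(2p̄(1 − p̄)/n) ] / √( p0(1 − p0)/n + p1(1 − p1)/n ) }

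With n = 5,000, 80% power is reached at RR 1.639 for p0 = 1% and RR 1.069 for p0 = 40%. These round to 1.6 and 1.1. The stated range is reproduced with no design effect.

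**Step 2: unit-level exposure, 10,000 admissions.** Design effect DE = 1 + (m − 1) × ICC, with n replaced by 5,000 / DE. At m = 93.2 the 10,000 infants come from about 107 units (10,000 / 93.2).

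| Outcome | Assumed ICC | DE | Effective N | Detectable RR | Power at stated RR |
|---|---|---|---|---|---|
| 1% | 0.001 | 1.09 | 9,156 | 1.67 | 72% |
| 1% | 0.0025 | 1.23 | 8,126 | 1.72 | 67% |
| 1% | 0.01 | 1.92 | 5,202 | 1.93 | 48% |
| 40% | 0.01 | 1.92 | 5,202 | 1.10 | 83% |
| 40% | 0.02 | 2.84 | 3,516 | 1.12 | 67% |
| 40% | 0.05 | 5.61 | 1,782 | 1.16 | 40% |

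The last column uses RR 1.6 at 1% and RR 1.1 at 40%. With no clustering these powers are 75% and 98%; both depart from 80% only because the RRs were rounded to one decimal.

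**Step 3: which ICCs are plausible at each incidence.** On the proportion scale, between-unit SD = √(ICC × p(1 − p)). At p = 1%, ICC 0.0025 gives √(0.0025 × 0.0099) = 0.5 percentage points, half the mean rate. ICC 0.01 gives 1.0 point, as large as the mean rate, which is extreme. At p = 40%, ICC 0.01 gives √(0.01 × 0.24) = 4.9 points and ICC 0.05 gives 11 points. The two ends therefore need different ICC ranges.

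**Step 4: other readings of the sample.**

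- *10,000 spread over all 251 units* (m = 39.8). At 40% incidence, ICC 0.01 / 0.02 / 0.05 gives detectable RRs of 1.08 / 1.09 / 1.12. RR 1.1 keeps 80% power up to ICC about 0.028, against about 0.012 at 93 per unit.
- *All 23,400 yearly admissions* (m = 93.2). RR 1.6 at 1% needs 2 × 5,594 = 11,188 independent infants, so the largest tolerable DE is 23,400 / 11,188 = 2.09 and the ICC limit is 1.09 / 92.2 = 0.012. RR 1.1 at 40% needs 2 × 2,389 = 4,778, so the largest DE is 4.90 and the ICC limit is 3.90 / 92.2 = 0.042.
- *Four years of all admissions* (93,600; m = 373 in the same units). The largest DEs are 8.37 and 19.59, so the limits are 7.37 / 371.9 = 0.020 and 18.59 / 371.9 = 0.050. Quadrupling the infants raises the limits only modestly, because no units are added.

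**The case against.** The strongest reply has four parts.

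- **The sample is understated.** The 10,000 admissions are about 43% of the yearly total in Table 1 (10,000 / 23,400), which absorbs a design effect of about 2. This stands: with all admissions the stated relative risks survive ICCs up to about 0.012 and 0.042. It is not, however, the reason the article gives, and it does not cover larger ICCs.
- **Exposures are mixed.** The type of initial respiratory support, surfactant timing and inborn status can differ between infants in one unit and do not carry the full design effect. This also stands, and it limits the point to exposures shared by the unit.
- **The analysis handles clustering.** Random-effects models are planned, so no estimate or error rate is affected. Correct: only the power statement is at issue.
- **One-decimal rounding is not an error.** RR 1.64 was rounded down and 1.07 up. Agreed: 1.6 needs no correction.

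A reader might go further and infer that relative risks of 1.6 to 1.1 cannot be detected with 80% power. The document does not support that. It gives no ICC, and RR 1.1 at 40% incidence keeps 83% power at ICC 0.01 even with 10,000 admissions. A reader might also apply an ICC of 0.05 to a 1% outcome and find a detectable RR of 2.81, but that implies a between-unit SD 2.2 times the mean rate. Nor does the article say that null findings will be read as absence of effect; it acts on associations that are found.

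**Conclusion.** The point holds in a limited form. The stated range is the independent-infant result, and for factors shared by all infants in a unit the calculation omits the design effect. Calling it conservative on the strength of a one-year window is not supported for those factors.

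The size is conditional on the ICC. With 10,000 admissions at 93 per unit, the detectable relative risk for a 1% outcome moves from 1.64 to between 1.67 and 1.72 at ICCs of 0.001 to 0.0025, and to 1.93 at the extreme value of 0.01. For a 40% outcome it moves from 1.07 to between 1.10 and 1.16 at ICCs of 0.01 to 0.05.

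These figures assume equal unit sizes and no network-level clustering. Table 1 shows unequal volumes (for example 3,700 / 73 = 51 admissions per unit in Japan and 7,700 / 44 = 175 in the UK network). Both simplifications favour the plan.

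**What to change.** In the power paragraph:

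1. Delete the word conservative, or confine it explicitly to the one-year window.
2. State that the current figures apply to treatments that vary between infants within a unit. Leave 1.6 and 1.1 as they are.
3. Add detectable relative risks for unit-level exposures, giving the number of NICUs, the infants per unit-year and a separate ICC range for each outcome, estimated from the 2007–2010 data.
4. Say whether 10,000 or all 23,400 yearly admissions are assumed, since the answer depends on it.

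The cost is a few sentences and one ICC estimate per outcome from data already planned for collection. The stated figures for unit-level exposures become somewhat less favourable; design and analysis do not change.
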